### **14.4 Analysis of safety**

Safety will be assessed and the incidence of safety events will be analyzed using descriptive statistics. Safety events include ROP of any stage, (IVH, NEC, BPD, LOS, and colorectal and anal injuries, and death.

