### **8.2 Secondary end-points**

(1) Stage II or III necrotizing enterocolitis (NEC, Bell standard)

(2) Hospitalization days

(3) Body weight at discharge

(4) Duration of total parenteral nutrition

(5) Cholestasis(Serum binding bilirubin concentration > 1.0 mg/dL (17.1 mmol/L)

Serum total bilirubin < 5.0 mg/dL (85.5 mmol/L) or >20%

Total bilirubin concentration >5.0 mg/dL (85.5 mmol/L), measured 2 weeks after birth in two groups

(6) Any adverse events reported: nosocomial infection, nosocomial death, retinopathy of prematurity (ROP, any stage), chronic lung disease (CLD), requirement of ventilatory support or oxygen after a corrected gestational age of 36 weeks, intraventricular hemorrhage (IVH, grade 2 and above), bronchopulmonary dysplasia (BPD), late-onset sepsis (LOS), diarrhea, colon perforation, malabsorption, rectal bleeding, and rectal trauma.

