### **14.3 Analysis of Secondary Outcomes**

The secondary outcomes will include the hospitalisation days, weight at the time of discharge, and duration of TPN. The outcomes will be analyzed using an independent sample t-test or Mann–Whitney test. Meanwhile, a multiple linear regression model will be used to analyze the factors affecting primary outcomes, including gender, birth weight, history of a mother's disease, etc. Outcomes are presented as median (IQR). For outcome differences between the treatment and control arms, the median difference and 95% CI will be assessed using the Mann–Whitney U test and the Hodges–Lehmann method.

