## 15. Discussion

Due to the large number of premature infants being born worldwide, countries are facing an enormous medical burden. Feeding is a significant challenge for premature infants and establishing full enteral feeding is an important goal in their care. Earlier full enteral feeding is associated with fewer failures of postpartum growth. Unfortunately, any delay in meconium excretion is related to a delay in transition to full enteral feeding. Compared with term infants, many premature infants pass the first meconium only after considerable delay. Times for the evacuation of the first and last meconium is critical for gastrointestinal function and feeding tolerance. If meconium evacuation can be expedited through the use of an effective enema, this may lead to a faster transition to full enteral feeding and a decreased reliance on intravenous nutrition. However, the available evidence is inconclusive. In contrast to other enemas, the amount of magnesium salts in breast milk is high and relatively stable, which can promote gastrointestinal peristalsis and help meconium evacuation[21,22]. In addition, breast milk can reduce the risk of enterovirus infection and balance the intestinal flora of premature infants[23,24]. Therefore, the trial will collect all participants' data to determine whether this trial has potential clinical significance and can provide reliable evidence for clinical intervention. The results may yield a new, safe, inexpensive, and easy-to-use intervention to effectively evacuate meconium in preterm infants.

To the best of our knowledge, the major strength of this randomized controlled trial is to evaluate, for the first time, the effectiveness of a breast milk enema in promoting complete meconium evacuation and reach full enteral feeding among preterm and extremely preterm infants. Consequently, the results will provide critical information regarding a new enema to effectively evacuate meconium in preterm infants.

The study protocol has several limitations. First, some infants achieving complete meconium evacuation may withdraw before observing the time to reach full enteral feeding. We will further analyze and design a more comprehensive investigation

482 based on this study. Second, this trial is a single-center clinical trial. Therefore, the  
483 representativeness of the participants is limited to some extent. Finally, some mothers  
484 may be unable to produce enough breast milk in early postpartum, which may slow  

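### NEC stage II/III is the first secondary end-point, yet the plan gives it descriptive incidence only, with no between-arm estimate or confidence interval

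*Protocol*

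**What the plan says.** Section 8.2 opens its list of secondary end-points with "Stage II or III necrotizing enterocolitis (NEC, Bell standard". Items (2) to (4) are hospital stay, discharge weight and duration of parenteral nutrition. Item (6) is a list of adverse events.

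Section 14.3 then says: "The secondary outcomes will include the hospitalisation days, weight at the time of discharge, and duration of TPN". NEC is not among them, and the methods given there suit continuous outcomes only. For those outcomes, "the median difference and 95% CI will be assessed using the Mann–Whitney U test and the Hodges–Lehmann method".

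NEC returns in section 14.4, without the stage II/III qualifier: "Safety events include ROP of any stage, (IVH, NEC, BPD, LOS, and colorectal and anal injuries, and death". The method stated for this whole group is that "the incidence of safety events will be analyzed using descriptive statistics". No contrast between arms, interval or upper bound is mentioned.

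The Discussion (section 15) hopes that "The results may yield a new, safe, inexpensive, and easy-to-use intervention" will come of the trial.

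**The concern.** A named secondary end-point should have an analysis that estimates the effect of treatment on it. Here the first on the list has none, while the three that follow it do. Nothing in the protocol explains the difference, and section 14 carries the heading of a statistical analysis plan, so the descriptive method is a stated choice and not a blank.

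The consequence lies in interpretation. Two incidences printed side by side, with no interval, invite the reader to take similar numbers as reassurance. The sample was sized on time to complete meconium evacuation alone, so similar or even zero counts can coexist with an excess of NEC or rectal injury that neonatologists would regard as important. If the word safe is later used, the plan supplies only raw incidences to support it.

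**Working it through.** **Sample size (protocol section 11).** The inputs are a two-sided α of 0.05, power 0.80, SD 2 days, differences of 1.4 and 1.2 days, and 1:1 allocation. Per arm, n = 2(1.96 + 0.842)² × 2² / difference².
- 1.4 days: 32.04, so 33 per arm, 66 in total (stated 64).
- 1.2 days: 43.6, so 44 per arm, 88 in total (stated 88).
- Dividing the stated totals by 0.8 for loss gives 80 (stated 78) and 110 (stated 108).

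The plan's figures are reproduced to within two infants. The total is 78 + 108 + 108 = 294, or 147 per arm. Before the allowance for loss it is 64 + 88 + 88 = 240, or 120 per arm. No safety event enters this calculation.

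**What similar NEC counts would leave open.** The documents give no NEC rate, so about 5% and about 10% in each arm are assumed. The risk-difference interval is Newcombe's, built from the Wilson limits l and u of each arm. With equal proportions p in both arms, its upper limit is √[(u − p)² + (p − l)²]. The risk-ratio limit uses the log method, exp(1.96 × √[2(1/x − 1/n)]).

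For 7/147 in each arm:
- p = 0.0476, l = 0.0233, u = 0.0950.
- Risk difference: √(0.0474² + 0.0244²) = 0.053.
- Risk ratio: √[2(1/7 − 1/147)] = 0.522, and exp(1.96 × 0.522) = 2.8.

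For 15/147 in each arm:
- p = 0.1020, l = 0.0628, u = 0.1615.
- Risk difference: √(0.0595² + 0.0392²) = 0.071.
- Risk ratio: √[2(1/15 − 1/147)] = 0.346, and exp(1.96 × 0.346) = 2.0.

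| Events in each arm | Upper 95% limit, risk difference | Upper 95% limit, risk ratio |
|---|---|---|
| 7/147 | +5.3 points | 2.8 |
| 15/147 | +7.1 points | 2.0 |
| 6/120 | +6.1 points | 3.0 |
| 12/120 | +7.9 points | 2.1 |

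**Zero events.** The exact two-sided 95% upper limit for one arm is 1 − 0.025^(1/n).
- n = 147: 2.5%.
- n = 120: 3.0%.
- n = 39 (half of the 78 infants in the youngest stratum, for which section 14.5 repeats the analyses): 9.0%.

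**The case against.** Descriptive incidence by arm is common for adverse events in a trial sized for efficacy. Item (6) of section 8.2 also lists adverse events as secondary end-points, so the protocol may simply treat NEC as one more harm and handle it under 14.4. Section 14.4 does not forbid risk differences, and a separate SAP, not shown here, could add them. Monthly safety-committee meetings (12.1) and the recording of all adverse events with causality (12.2) also bear on safety.

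Much of this stands for the rarer adverse events, and it means that one cannot say the NEC effect will never be estimated. It does not remove the mismatch. NEC is listed separately from item (6), ahead of outcomes that do receive an estimate. Section 14 itself fixes the weaker method. Monitoring during the trial does not supply a final comparison.

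Two stronger readings are tempting, and the documents do not support them.

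- A reader might infer that, because reporting is descriptive, a doubling of NEC would usually be missed. Power is set by the sample size and event rate, and an interval would not raise it. The inference also needs a control rate that the documents do not give. By the normal approximation for two proportions (two-sided 5%), the power to detect a doubling with 147 / 120 per arm is 37% / 31% from 5% to 10%, but 67% / 58% from 10% to 20%. It passes 50% at a control rate of about 7.0% / 8.4%.
- A reader might infer that the trial sets out to declare the enema safe. The sentence in section 15 expresses a hope. Safety is not among the three objectives in section 2, and no safety hypothesis or margin is stated, so the lack of a margin is not a fault.

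**Conclusion.** The point holds as an inconsistency between sections 8.2, 14.3 and 14.4. The first-listed secondary end-point has no planned between-arm estimate or interval, while end-points (2) to (4) have both. This rests on the text alone and needs no assumption.

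Its practical size depends on assumed NEC rates. At equal incidences of about 5% to 10%, an interval would still admit an excess of roughly 5 to 7 points with 147 per arm, or 6 to 8 points with 120. Descriptive reporting would leave that uncertainty out of sight. The finding concerns what is reported and how it may be read. It does not show that the trial is too small for its purpose, or that its authors will overstate safety.

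**What to change.** In 14.3, list NEC stage II/III, with the same stage definition as in 8.2, and give it a risk difference (milk minus saline) with a 95% confidence interval, for example by Newcombe's method. Carry the stage qualifier into 14.4.

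In 14.4, give the same estimate and interval for death, late-onset sepsis and colorectal or anal injury. Where an arm has no events, add the exact upper limit for that arm. The remaining adverse events can stay descriptive.

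State that any remark on safety will be worded by the upper confidence limit, that is, by the size of excess that the data exclude, and not by the lack of a visible or significant difference.

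The cost is a few sentences of analysis wording, using data already to be collected. The intervals will be wide, and any safety statement will have to be qualified. The change makes the uncertainty visible; it adds no power.

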### **14.5 Subgroup Analysis**

For all aforementioned statistical analyses, stratified subgroup analyses will be conducted based on gestational age to compare specific intra-group outcomes. Gestational age categories are 23 weeks  $\leq$  gestational age < 28 weeks, 28 weeks  $\leq$  gestational age < 29 weeks and 29weeks  $\leq$  gestational age < 30 weeks This approach is employed to assess nuanced differences within distinct gestational age subgroups, enabling a comprehensive evaluation of outcomes tailored to the developmental stage of the fetus.

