### **5. Randomization**

Participants will be allocated to intervention and control groups with stratified block randomization using a computer-generated randomization list by an independent statistician not otherwise involved in the trial. The participants will be stratified based on gestational age. Then, the participants will be assigned in a randomized block design to the intervention and control groups in a 1:1 ratio. Block size will be 4 and 6 to ensure equal numbers of participants in the intervention and control groups. At the beginning of the trial, random sequence will generate a set of study numbers. Each study number will be paired with a method of intervention and sealed in an opaque envelope. The envelopes will be grouped based on gestational age. Recruited

participants will be allocated to intervention or control groups by selecting an envelope. The program will be set up using SAS 9.2 (SAS Institute Inc., Cary, NC).

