## **11. Sample size and statistical power estimation**

The sample size estimate is based on our pilot study; the time of complete meconium evacuation was 1.4 days, 1.2 days, and 1.2 days earlier in the breast milk enema group than in the saline enema group at  $23 \text{ w} \leq \text{gestational age} < 28 \text{ w}$ ,  $28 \text{ w} \leq$

gestational age < 29 w, and 29 w  $\leq$  gestational age < 30 w, respectively. Given that  $\alpha = 0.05$ ,  $\beta = 0.2$ , standard deviation (SD) = 2, sampling ratio = 1 and taking a 20% drop rate into account, the required total sample size is 78, 108, and 108 premature infants in each gestational age, respectively. A website was used to calculate the sample size (<http://powerandsamplesize.com/Calculators/>).

| Gestational age               | Difference | $\alpha$ | $\beta$ | SD | Sample size | Loss of follow-up | Final sample size |
|-------------------------------|------------|----------|---------|----|-------------|-------------------|-------------------|
| 23W $\leq$ Gastinal age < 28W | 1.4d       | 0.05     | 0.2     | 2  | 64          | 20%               | 78                |
| 28W $\leq$ Gastinal age < 29W | 1.2d       | 0.05     | 0.2     | 2  | 88          | 20%               | 108               |
| 29W $\leq$ Gastinal age < 30W | 1.2d       | 0.05     | 0.2     | 2  | 88          | 20%               | 108               |

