### **14.6 Statistical software**

A two-sided  $P < 0.05$  will be considered statistically significant. All analysis will be performed in SAS version 9.2 (SAS Institute Inc., Cary, NC, USA) and SPSS version 22.0 (IBM Inc., Chicago, IL, USA) software. Interim analyses are not planned.

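### Section 14.5 tests each gestational-age stratum separately and names no test of whether the treatment effect differs between strata, so it cannot support an age-dependent claim

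*Protocol*

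**What the plan says.** Protocol section 14.5 extends every preceding analysis to three gestational-age bands (23 to under 28, 28 to under 29, and 29 to under 30 weeks). It says that "stratified subgroup analyses will be conducted based on gestational age to compare specific intra-group outcomes" and gives the purpose as "to assess nuanced differences within distinct gestational age subgroups", with an evaluation suited to developmental stage.

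The analyses carried into each band come from sections 14.2 and 14.3: t-test or Mann–Whitney, Hodges–Lehmann median difference with 95% CI, and, for the primary outcomes, Kaplan–Meier curves with log-rank tests. The regression named there lists prognostic factors such as sex, birth weight and maternal disease, and no arm-by-gestational-age term. Section 14.6 gives a single threshold: "A two-sided $P < 0.05$ will be considered statistically significant".

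Section 11 sizes each band on its own. It expects complete meconium evacuation "1.4 days, 1.2 days, and 1.2 days earlier in the breast milk enema group than in the saline enema group" in the three bands, with "standard deviation (SD) = 2, sampling ratio = 1 and taking a 20% drop rate into account", and concludes that "the required total sample size is 78, 108, and 108 premature infants in each gestational age, respectively". Section 5 stratifies randomization by gestational age.

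**The concern.** Three parallel significance verdicts invite a reader to set them side by side. A significant result in one band next to a non-significant one in another looks like an effect that depends on maturity, and section 14.5's reference to developmental stage encourages that reading. The pattern is also what chance produces when the effect is identical in all bands, since each band has an appreciable probability of missing a real effect. Without a direct test of the difference between bands, the protocol gives no basis for telling the two situations apart. At stake is whether the trial reports that the enema works at some gestational ages and not at others without evidence for it.

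**Working it through.** **Inputs.** From section 11: SD 2 days, alpha 0.05, power 80%, allocation 1:1, expected differences 1.4, 1.2 and 1.2 days, totals 64/88/88 before loss and 78/108/108 after. Per arm this is 32/44/44 and 39/54/54. Two-sidedness is from section 14.6. A common true effect is an assumption: 1.2 days as the central case, with 1.0 and 1.4 days as the range.

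**1. The plan's own figures.** n per arm = 2(1.960 + 0.842)² × SD² / difference².
- 1.4 days: 2 × 7.849 × 4 / 1.96 = 32.04, total about 64.
- 1.2 days: 2 × 7.849 × 4 / 1.44 = 43.60, so 44, total 88.

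These match the stated 64 and 88. Dividing by 0.8 for loss gives 80 and 110, close to the stated 78 and 108. Each stratum is therefore sized at about 80% power for meconium evacuation.

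**2. How often strata disagree under one common effect of 1.2 days.** Power is that of the two-sided t-test with 2n − 2 df and noncentrality 1.2 / (2√(2/n)).
- 32/44/44 per arm: noncentrality 2.40, 2.81, 2.81; power 0.656, 0.795, 0.795. All three significant: 0.656 × 0.795² = 0.414. None: 0.344 × 0.205² = 0.014. Mixed: 1 − 0.414 − 0.014 = **0.57**.
- 39/54/54 per arm: noncentrality 2.65, 3.12, 3.12; power 0.744, 0.871, 0.871. All: 0.564. None: 0.004. Mixed: **0.43**.

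A simulation of 20,000 trials gave 57% and 43%. A normal approximation gives 55% and 42%.

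**3. Range over the common effect.** Probability of a mixed verdict:

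| Common effect | 32/44/44 per arm | 39/54/54 per arm |
|---|---|---|
| 1.0 d | 73% | 66% |
| 1.2 d | 57% | 43% |
| 1.4 d | 36% | 22% |

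**4. The direct test.** In the same simulations at 1.2 days, a 2-df test of heterogeneity across strata at the 5% level wrongly signalled a difference in 5.3% (32/44/44) and 5.0% (39/54/54) of trials.

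**5. What the direct test can detect.** The variance of a stratum's arm difference is 2 × SD² / n = 8/n. For the youngest stratum against the two older ones combined:
- 32 against 88 per arm: SE = √(8/32 + 8/88) = 0.584; difference detectable with 80% power = 2.80 × 0.584 = 1.6 days.
- 39 against 108 per arm: SE = √(8/39 + 8/108) = 0.528; detectable difference = 1.5 days.

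Power for the design's own difference of 1.4 − 1.2 = 0.2 days is 6.4% and 6.7%. This is a 1-df contrast; the 2-df test does slightly worse, at about 6%.

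**The case against.** The strongest reply is that section 14.5 does not claim to compare strata. Its wording concerns differences within each band, and within-stratum tests answer that question. A reader might infer that the protocol plans to declare an age-dependent effect from separate P values, or that its method fails the question it sets. The text supports neither: no sentence says the strata will be compared. Side-by-side reading is a likely use, not a written rule. This stands and limits the point to what the analyses can support.

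A second reply is that these are not exploratory cuts. Randomization is stratified by gestational age and each band has its own sample size. A reader might infer that the stratum results should be demoted to description and efficacy taken only from the overall estimate. That would change the structure implied by section 11, and the lack of an interaction test does not require it. Stratum effects with 95% CIs are also already planned, so the plan is not a set of bare P values.

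Third, the interaction test is weak: it needs a difference between strata larger than any treatment effect the trial expects. That is true. It calls for caution with a null interaction result, but it does not make separate verdicts better evidence of a difference.

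Finally, a separate SAP, not shown here, might add the test. But section 14 of the protocol is itself headed as the statistical analysis plan and says how gestational age will be examined, so the guard belongs there.

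**Conclusion.** The point holds in this limited form. The within-stratum comparisons are valid for what they estimate, but as written nothing in the protocol could support a statement that the effect varies with gestational age. At the planned sizes and a common effect of 1.2 days, contradictory verdicts across strata are about as likely as not (57% or 43%), with 22% to 73% over effects of 1.4 to 1.0 days; a direct test would err in about 5%.

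These figures assume normal outcomes with SD 2 days, equal arms within each stratum, and t-tests. They apply to time to complete meconium evacuation. Section 11 gives no effect or SD for time to full enteral feeding, so no figure can be given for that outcome, although the reasoning is the same.

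Two other figures are tempting. The first is 1 − 0.8³ = 49%, the chance of at least one non-significant stratum at nominal power. It rests on planned effects that are not equal, and it includes trials where every stratum fails, so it does not measure false disagreement under one effect. The second is 1 − 0.95³ = 14%, the chance of at least one significant stratum when there is no effect. That is mainly a multiplicity matter and does not measure the lack of an interaction test.

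**What to change.** Amend section 14.5 in three ways.

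1. Keep the stratum-specific estimates with their planned 95% CIs.
2. For each primary outcome, add one model with arm, gestational-age stratum and their interaction, and report the 2-df interaction test. The linear regression already named in section 14.2 can carry these terms and gives effects in days, the scale of section 11. If a time-to-event model is preferred, name it in advance.
3. State that any claim of a differing effect by gestational age rests on the interaction test, and not on significance in one stratum beside non-significance in another. Add that a non-significant interaction does not show equal effects, given a detectable difference of about 1.5 to 1.6 days.

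The cost is one added model per primary outcome and a few sentences. Gestational age is already recorded at baseline and used in randomization, so no new data or participants are needed. The price is that the trial will rarely be able to confirm a modest real difference between strata; separate tests could not confirm one either.

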### **14.6 Statistical software**

A two-sided  $P < 0.05$  will be considered statistically significant. All analysis will be performed in SAS version 9.2 (SAS Institute Inc., Cary, NC, USA) and SPSS version 22.0 (IBM Inc., Chicago, IL, USA) software. Interim analyses are not planned.

## 15. Discussion

Due to the large number of premature infants being born worldwide, countries are facing an enormous medical burden. Feeding is a significant challenge for premature infants and establishing full enteral feeding is an important goal in their care. Earlier full enteral feeding is associated with fewer failures of postpartum growth. Unfortunately, any delay in meconium excretion is related to a delay in transition to full enteral feeding. Compared with term infants, many premature infants pass the first meconium only after considerable delay. Times for the evacuation of the first and last meconium is critical for gastrointestinal function and feeding tolerance. If meconium evacuation can be expedited through the use of an effective enema, this may lead to a faster transition to full enteral feeding and a decreased reliance on intravenous nutrition. However, the available evidence is inconclusive. In contrast to other enemas, the amount of magnesium salts in breast milk is high and relatively stable, which can promote gastrointestinal peristalsis and help meconium evacuation[21,22]. In addition, breast milk can reduce the risk of enterovirus infection and balance the intestinal flora of premature infants[23,24]. Therefore, the trial will collect all participants' data to determine whether this trial has potential clinical significance and can provide reliable evidence for clinical intervention. The results may yield a new, safe, inexpensive, and easy-to-use intervention to effectively evacuate meconium in preterm infants.

To the best of our knowledge, the major strength of this randomized controlled trial is to evaluate, for the first time, the effectiveness of a breast milk enema in promoting complete meconium evacuation and reach full enteral feeding among preterm and extremely preterm infants. Consequently, the results will provide critical information regarding a new enema to effectively evacuate meconium in preterm infants.

The study protocol has several limitations. First, some infants achieving complete meconium evacuation may withdraw before observing the time to reach full enteral feeding. We will further analyze and design a more comprehensive investigation

482 based on this study. Second, this trial is a single-center clinical trial. Therefore, the  
483 representativeness of the participants is limited to some extent. Finally, some mothers  
484 may be unable to produce enough breast milk in early postpartum, which may slow  
485 down trial progress and prolong the time to recruit the estimated sample size.

486

